# 4. INVESTIGATIONAL PLAN

## 4.1 Overall study design and plan description

This is a prospective, single centre, double-blind, randomised, parallel, placebo-controlled, comparative study.

Two hundred and forty eight patients, aged at least 55 and less than 85, presenting neovascular age-related degeneration in one eye and lesions of age related maculopathy (confluent and diffuse hard drusen or /and soft drusen with or without pigmentary changes or/and reticular pseudodrusen) in the second eye (study eye), are planned to be included in one centre.

Randomisation will be balanced for each treatment arm. The total treatment duration for each patient will be 3 years.

Five visits are planned, a screening visit at D0 and four follow up visits at 6 months and at the end of Year 1, Year 2 and Year 3.

This study will bring a direct individual benefit for patients.

Age-related macular degeneration is a leading cause of visual handicap. Its impact on our growing elderly population is rising. Nevertheless, there is no reference treatment to prevent further age-related macular degeneration and therapeutic options are very limited.

Based on results of epidemiological studies in age-related macular disease and based on clinical proofs of its efficacy on cardiovascular or inflammatory diseases, DHA oral supplementation seems to be an attractive and safe preventive therapeutic option for age-related macular degeneration. DHA is likely to delay the occurrence of choroidal new vessels (i.e. occurrence of a severe visual impairment) in patients presenting with early stages of the disease.

Moreover, for all patients, progression of the disease will be regularly evaluated according to the protocol recommended by the AMD specialists (frequency of follow-up visits and performed examinations). This will allow the early detection and required treatment (laser or photodynamic therapy) of choroidal new vessels in order to reduce, as much as possible, the risk for later severe visual loss.

## 4.2 Rationale for study design

AMD is a chronic degenerative disease of the macular region of the retina.

The long treatment duration required in this study (3 years), is suitable for the evaluation of a DHA supplementation as a preventive treatment for AMD. It takes into account the percentage of new vessels occurrence that is around 30 to 36 % in the studied population after 3 years (see section 8.2).

The study design involving two parallel groups is the most suitable for a comparative trial (on an evolutive disease) that requires such a long treatment duration.

Since there is no reference treatment to prevent further AMD it is justified to use a placebo as a comparative treatment. Olive oil is chosen because it is part of a staple diet and has no deleterious effect on the retina.

In the general population the recommended nutritional daily intake of DHA are 120 mg daily.

A preliminary study (NAT 1) has shown that it is possible to significantly increase cell membrane level of DHA in aged population, by an oral intake of 480 mg of DHA (23) .

Since cardiovascular studies did not show any adverse event until the dose of 3g per day of DHA and EPA (21), and knowing that a pharmacological effect is searched in the elderly whose retina is already affected, our purpose is to enhance DHA daily intake and to be close to the 1 g daily level.

Taking into account a number of daily units (3 capsules per day) compatible with a good compliance the chosen DHA daily dose for this study is 840 mg (equivalent to eating 50-100g of fish).

Furthermore, as previously mentioned, the risk for exudative AMD has been associated with polymorphism in the gene encoding apoE : a lower frequency of epsilon 4 allele carriers was found in patients suffering from exudative AMD (5).

Consequently apoE genotype of consenting patients will be evaluated and the efficacy of the treatment with DHA will be assessed considering the apoE genotype.

## 4.3 Selection of study population

### 4.3.1 Inclusion criteria

Eligible patients have to fulfil the following criteria:

1. Male or female outpatients aged  55 years and < 85 years,
2. Having given written informed consent,
3. Presenting neovascular age-related macular degeneration in one eye,
4. With lesions of age related maculopathy (confluent and diffuse hard drusen or/and soft drusen with or without pigmentary changes or/and reticular pseudodrusen) and with minimal visual acuity of +0.3 LogMAR ( 5/10) in the fellow eye (study eye),
5. Likely to attend the follow-up visits during all the study period.

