To date, etiology of AMD remains unclear. AMD appears to be a multifactorial disease. Several environmental risk factors have been evidenced, including smoking, elevated serum cholesterol levels and systemic hypertension (1). However, a number of studies suggest that AMD has a familial component and that genetic factors contribute to its development. The 4 allele of the gene coding for apoE (an apolipoprotein involved in the transport of cholesterol and lipids) has been shown to have a protective effect on the occurrence of exudative AMD (soft drusen and choroidal new vessels) (1, 5). These findings evidenced the role of the metabolism of lipids in AMD and leaded us to investigate this pathway. Four recent independent epidemiological studies have shown a significant relationship between high intake of docosahexaenoic acid 22:6 omega 3 (DHA), a long chain poly-unsaturated fatty acid which is predominantly found in oily fish, and a decreased risk of neovascular AMD (6, 7, 8, 9). Furthermore, exudative AMD is less frequent in populations whose nutritional diet is rich in fish and AMD has begun to appear in Iceland or Japan with the shift to a more westernised diet (10). DHA appears to play an important role in the normal development, morphology and function of the retina (11, 12, 13,14). In animals (rats, guinea pig), dietary deficiency in omega 3 fatty acids has been associated with altered function of the retina. Interestingly, impaired vision due to a long period of DHA deprivation remains reversible with a DHA enriched diet. More recently studies in infants, prematured or not, have confirmed the essential role of DHA for the functional development of the retina in human (12 ).

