### 5.2.2.Drug dispensation

1 randomisation list will be established and balanced for treatments. The treatments will be continuously numbered from 001 to 248.

At the end of the baseline evaluation, treatment numbers will be allocated to the patients in ascending order using the next available consecutive number of the list.

The first patient will so receive pack 001 , the second pack 002 and then consecutively.

The double-masked treatment will be dispensed by the investigator or the pharmacist.

3 dispensations will be done during the study:

- First dispensation on D0, at the end of the baseline visit (Visit 1).
- Second dispensation 1 year later, at the end of Visit 3 (Year 1 visit).
- Third dispensation 1 year later, at the end of visit 4 (Year 2 visit).

Each time the patient will receive a package containing 20 boxes of 60 capsules, that is to say 1200 capsules for a 1 year treatment.

Upon each dispensation, the duplicate label provided must be fixed on the corresponding case report form or on a dispensation form.

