## 5.4 Randomisation and code-breaking

The randomisation list will be prepared prior to the enrolment using the QL-Ranclin software.

Treatments will be balanced in a 1 to 1 ratio.

At the end of the baseline visit (Day 0), patients who fulfilled all inclusion criteria and none of the exclusion criteria will be randomly assigned to one of the treatment groups (DHA or placebo).

Only in emergencies, and for reasons which must always be given, can the code be broken.

For this purpose sealed opaque envelopes, bearing the number of the patient and containing the name of the allocated treatment, will be given to the investigator or the pharmacist.

It is thus possible to unmask the treatment of one patient only without unmasking all the others.

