### Secondary efficacy variables

Fundus photographs (red free frame), performed through the dilated pupil, will allow :

- first to describe the type, number, size and area of drusen on D0,
- then to evaluate the occurrence and progession of drusen (number, size and area), in the study eye, at each follow-up visit.

For this purpose, an automatic quantification of drusen will be performed by LERISS laboratory using an image enhancement and automatic detection and quantification of drusen software. The protocol for quantification and evaluation of evolution of drusen is described in appendix I. B.

Change in visual acuity will be evaluated from baseline using the ETDRS charts. Best corrected visual acuity will be evaluated, before pupil dilatation, by the same person at each visit. The protocol for evaluation of visual acuity is given in appendix I. A.

A significant decrease in visual acuity is defined as a decrease of more than 15 letters at ETDRS.

Multifocal ERG modification from baseline will be evaluated yearly on the study eye. ERG responses will be obtained from the anesthetized cornea, through the dilated pupil, with a bipolar contact lens electrode (see appendix I.G). ERG must be performed before fundus photographs and angiography.

DHA concentration in red blood cell membranes (RBCM) will be performed on D0, at the 6 month visit and at the 3 year visit. For this purpose, 5 ml of 12 hour fasting blood samples will be taken in the early morning. DHA concentration change in red blood cell membrane is considered as the witness of the DHA ability to penetrate the retina visual cells*.* The protocol for dosage of fatty acids in RBCM is given in appendix I.D.

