Extent of exposure will be calculated as the number of days on which the study medication has been taken.

Methods of analysis

Primary Efficacy Variable

The primary outcome of the study will be the time to occurrence of CNV in the study eye.

The occurrence rates in the 2 treatment groups will be compared using life-table methods.

The data will be analysed on an intent-to-treat principle so that data on time to occurrence of CNV is collected for all patients where possible, including early withdrawals from medication.

The difference between treatments will be tested using a log-rank test.

Prognostic factors which may affect the outcome, namely age, history of addiction to smoking, fish intake frequency, total cholesterol (TC) and APOE genotype will be considered for inclusion in the model.

Significance of these covariates, either time-dependent or time-independent, will be evaluated by proportional hazard model, the efficacy of the treatment will be adjusted by these covariates if necessary.

Data from patients withdrawn early will be considered censored at the point of withdrawal.

Secondary efficacy variables

The percentage of patients for whom CNV occur during the study will be compared between groups using a CHI square test or a Fisher test when required.

The change from baseline (time of enrollment ) in visual acuity scores at 6 months,Year 1, Year 2 and Year 3 will be compared between treatment groups by means of a Student t-test or a Wilcoxon Rank Sum test depending on data normality. The proportion of patients with a visual acuity decrease from baseline of more than 15 letters on ETDRS charts will be also compared across treatment groups using CHI square test or Fisher test.

The change from baseline in visual function (multifocal ERG),e.g change in amplitude and in timing, at Year 1, Year 2 and Year 3, will be compared between groups by means of a Student t-test or a Wilcoxon Rank sum test.

The progression of drusen (change from baseline in number, size and area) at 6 months, Year 1, Year 2 and year 3 will be compared between groups using a Wilcoxon Rank sum test .

The DHA concentration increase in red blood cells membrane at 6 months and at 3 years will be compared across groups using a Student t-test or a Wilcoxon test depending on data normality.

Safety variables

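### The primary analysis makes no planned use of study-eye lesion type, which eligibility leaves mixed and D0 photographs describe: forgone precision and no cover against chance imbalance, but no bias

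*Protocol*

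**What the plan says.** - **Eligibility (Protocol 4.3.1, criterion 4; repeated in the summary and 4.1).** The study eye must show "lesions of age related maculopathy (confluent and diffuse hard drusen or/and soft drusen with or without pigmentary changes or/and reticular pseudodrusen". The types are joined so that any one of them, or any combination, qualifies.
- **Allocation (5.2.2 and 5.4).** "1 randomisation list will be established and balanced for treatments", and "Treatments will be balanced in a 1 to 1 ratio". No stratification factor is named.
- **Primary test (8.1).** "The difference between treatments will be tested using a log-rank test". No stratum or covariate is attached to it.
- **Prognostic factors (8.1; the same five in the summary).** "Prognostic factors which may affect the outcome, namely age, history of addiction to smoking, fish intake frequency, total cholesterol (TC) and APOE genotype" are to be considered for a proportional hazards model, with adjustment only if judged necessary.
- **Baseline lesion data (6.1.3, secondary efficacy variables).** Fundus photographs serve "first to describe the type, number, size and area of drusen on D0".
- **Baseline comparability (8.1, other variables).** The arms are compared on D0 by significance tests. No consequence for the primary analysis is stated.

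**The concern.** The event is new vessels in the study eye, and the entry criterion lets that eye vary in lesion type. If lesion type predicts new vessels, the arms may differ by chance in their share of higher-risk eyes. Neither the log-rank test nor any of the five named covariates takes account of the study eye's condition. A D0 test that showed an imbalance would have no planned remedy, and adding the factor at that point would be data-driven.

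At stake is precision, and how the result can be read after an unlucky draw, in a single-centre trial of 248 patients planned at 80% power. The validity of the test is not at stake.

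**Working it through.** **1. The plan's own figure.** Inputs from 8.2: three-year risks 30% and 15%, two-sided 5%, 80% power, one year of recruitment, 20% drop-out.

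- Hazards per year: λ₁ = −ln(0.70)/3 = 0.1189 and λ₂ = −ln(0.85)/3 = 0.0542, so the hazard ratio is 0.456. Loss: η = −ln(0.80)/3 = 0.0744.
- Exponential-survival (Lachin–Foulkes) formula: N = 2·[1.96·√(2V(λ̄)) + 0.842·√(V(λ₁)+V(λ₂))]² / (λ₁−λ₂)². Here V(λ) = λ²/P(event), with uniform one-year entry and a common end at four years.
- Result: N = 244.2, rounded up to 245, as stated. One overall rate per arm is used, so the sample size does not depend on lesion type.

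**2. How large chance imbalance can be.** Assumption, not in the documents: half of the eyes are higher-risk. With 124 per arm, the arm difference in their share has SD √(2·0.25/124) = 0.0635, or 6.4 points, and 1.96 SD is 12.4 points. A difference of at least 10 points (10/6.35 = 1.57 SD) occurs in about 11% of trials.

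**3. What an imbalance does when DHA has no effect.** Assumption: overall three-year placebo risk stays at 30%.

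- A 12.4-point imbalance multiplied by a risk gap of 20, 30 or 40 points shifts the arm difference by 2.5, 3.7 or 5.0 points. The planned effect is 15 points.
- A 10-point imbalance gives an apparent hazard ratio of about 0.93, 0.90 or 0.88 (or its inverse) if eye types differ by a hazard ratio of 2, 3 or 4. For 3, the type-specific risks are 17.1% and 42.9%. The arms then have 0.55·17.1 + 0.45·42.9 = 28.7% and 0.45·17.1 + 0.55·42.9 = 31.3%, and ln(1−0.287)/ln(1−0.313) = 0.90.

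**4. Simulation by lesion hazard ratio.** Set-up: 248 patients, three years each, 20% exponential loss, treatment hazard ratio 0.456 within each eye type, 20,000 runs per scenario.

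| Lesion hazard ratio (assumed) | 2 | 3 | 4 |
|---|---|---|---|
| Overall type I error, unstratified | 5.0% | 5.0% | 5.1% |
| Overall power, unstratified / stratified | 77% / 77% | 75% / 78% | 75% / 79% |
| Type I error given imbalance ≥10 points, unstratified / stratified | 5.3% / 4.8% | 7.8% / 4.9% | 8.9% / 5.1% |
| Power, imbalance against DHA, unstratified / stratified | 68% / 78% | 59% / 78% | 55% / 81% |
| Power, imbalance favouring DHA, unstratified / stratified | 85% / 77% | 88% / 78% | 90% / 79% |

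Each directional row rests on about 5.5% of runs (about 1,100), so its Monte Carlo standard error is up to √(0.25/1,100) = 1.5 points.

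**5. Wider risk gaps.** Three-year placebo risks of 20% v 40%, 15% v 45% and 10% v 50% correspond to lesion hazard ratios of 2.3, 3.7 and 6.6. Stratifying gains about 1 to 6 points of power on average. Given an imbalance of at least 10 points, type I error is about 7–11% unstratified and near or below 5% stratified. With the imbalance against DHA, power is about 46–66% unstratified and about 75–86% stratified.

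**6. Is planned power lost?** A homogeneous population gives about 77% in this set-up, so 77% is the reference, not 80%. Applying 0.456 within each eye type moves the overall treated risk from 15% to 15.2%, 15.5% and 15.9%, a slightly smaller effect than planned. With the overall risks held at 30% and 15%, unstratified power is 78%, 77% and 78%, and stratified power is 79%, 81% and 84%. Nothing is lost against plan; stratifying adds to it.

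**The case against.** The strongest reply is that nothing here is wrong. A log-rank test after 1:1 randomisation is valid without strata, and its 5% error rate already allows for chance imbalance in every baseline factor. The planned 30% and 15% are overall rates and so absorb the case mix. The conditional figures describe about one trial in nine, under an assumed split and gradient. All of this stands.

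Three stronger readings are tempting, and the documents do not support them:

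- **That mixed eligibility biases the comparison or inflates type I error.** Overall type I error is 5.0–5.1% in step 4.
- **That heterogeneity takes power below plan.** Step 6 shows that it does not when the overall risks are as planned.
- **That the protocol itself ranks soft drusen as higher risk.** The introduction speaks of a "protective effect on the occurrence of exudative AMD (soft drusen and choroidal new vessels", but this describes the apoE allele. No section gives new-vessel risk by lesion type. The hard-drusen category is also limited to confluent and diffuse drusen, which narrows the range of eyes.

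It can also be said that covariates are usually settled in a SAP, which is not shown, and that 8.1 only promises to consider these factors. That is fair as far as it goes. However, 8.1 does give a specific list ("namely age, history of addiction to smoking, fish intake frequency, total cholesterol (TC) and APOE genotype will be considered for inclusion in the model"), the summary repeats it, and no study-eye factor is on it.

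**Conclusion.** The point holds as a missed, nearly free improvement, not as an error. Eligibility leaves lesion type mixed, and neither the randomisation, the primary test nor the named factors use it, although the D0 photographs describe the drusen.

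The average gain from using it is modest: about 1 to 6 points of power over the wider risk gaps, and close to nothing if the gradient is small or one lesion type dominates. The larger benefit is protection in the roughly 11% of trials with an imbalance of at least 10 points.

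Every size given rests on an assumed half-and-half split and an assumed risk gradient. The change is optional rather than essential.

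**What to change.** In section 8.1, add D0 study-eye drusen type as a pre-specified baseline factor for the primary comparison. Code it masked, before unblinding, from the D0 drusen description. Use it either as a stratum of the log-rank test or as a fixed baseline term in the proportional hazards model, and state which.

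Section 6.1.3 names drusen type, number, size and area, but not pigmentary change or pseudodrusen. Those two should enter the coding only if the D0 eligibility record captures them or they can be coded from the archived D0 images.

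The cost is a short addition to the text, one degree of freedom for a two-level factor and a small masked coding task. It needs no new visit, procedure or patient, and the sample size does not change.

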### 4.3.2 Exclusion criteria

Patients who met any of the exclusion criteria below were ineligible for study participation:

1. Choroidal new vessels in both eyes,
2. Wide central area of geographic atrophy encroaching on fovea, in the study eye,
3. History of other progressive ocular disease which may complicate the assessment of age-related macular degeneration (severe glaucoma, other severe retinopathy…),
4. Opacity precluding evaluation of retina photographs (cataract, corneal dystrophia…),
5. History of serious systemic disease which may prevent patient long term participation in the study (mental disorder, cancer, stroke…),
6. Patients treated with anticoagulants or predisposed to bleeding or haemorrhage,
7. History of an allergic reaction to fluorescein injection or to indocyanine green or to iodide,
8. Known sensitivity to DHA or vehicle,
9. Treatment with Maxepa or omega-3 polyunsaturated fatty acids within the previous 2 years,
10. Treatment with alpha-tocopherol acetate (vitamin E),
11. Any concomitant nutritional supplementation,
12. Involvement in the last 30 days in any other investigational drug study,
13. Drug abuse and/or excessive use of medications,
14. Patients who are unlikely to comply with the study protocol or who are likely to be moving and lost to follow up in the 3 years,
15. Monocular patients (for any other reason than age-related macular degeneration),
16. Patient not covered by the French Social Security scheme,
17. Patient being a ward of court.

### 4.3.3 Removal of patients from therapy or assessment

If a patient did not attend a scheduled control visit, he/she will be contacted again. In case of premature withdrawal from the study, the investigator is to make every effort to determine the reason.

Generally, patients may withdraw or be withdrawn from the study for the following reasons:

- Patient’s decision (in accordance with the Declaration of Helsinki, any patient can voluntarily discontinue the study at any time he or she chooses, without prejudice).
- If the investigator considers that the patient’s health is compromised by remaining in the study.
- If the patient is not sufficiently co-operative.
- If a serious adverse event prevents the patient from attending the follow-up visits.

# 5. TREATMENTS

## 5.1 Formula and presentation

Depending on the randomisation , the patient will receive one of the following treatments :

- Capsules containing 600 mg of fish oil comprising 280 mg of DHA*

| Fish oil  Comprising DHA  and EPA | 600 mg  280 mg  90 mg maximum |
| --- | --- |

*(* see also appendix IV concerning lawful regularity of the product)*

- Capsules of placebo

| Olive oil | 602 mg |
| --- | --- |

Excipient contains trace amount (2 mg) of alpha-tocopherol acetate (vitamin E) as conservative. It contains no allergic substance except for red iron oxide.

Both treatments will have identical presentation in order to preserve masking. Treatments will be supplied as capsules grouped in blister-pack of 20.

Each box will contain 3 blister-packs and so 60 capsules.

3 packages will be provided for each patient, each containing 20 boxes allowing a 1 year treatment.

Each blister-pack will be identified with the following legal mention:

- Sponsor ‘s name
- Study number
- Patient number
- Expiry date
- Use only under medical supervision

Moreover boxes will be labelled in accordance with European GMP, ICH guidelines and local requirements (article R.5123 in France) including:

- Study number

- Investigator’s name

- Patient number - For clinical trial use only

- 3 blister-packs of 20 capsules for oral route - Use only under medical supervision

- directions for use - Keep out of reach of children

- Storage : below 25°C; to shelter from light; - Return any empty packaging

to be kept dry and unused product

- Expiry date

- Sponsor’s name and address

In addition 2 duplicate labels will be provided on each patient package to be stuck on the case report form.

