Furthermore DHA is known to have specific retinal effects that are likely to play a preventive role in AMD, such as increase mitochondrial activity, increase RPE acid lipase activity, anti-oxydative , anti-proliferative and anti-apoptotic effects (20). DHA represents the main component (> 50%) of the lipids of the external membrane of the photoreceptors cells, suggesting a major role in the maintain of the structure of these cells. On the opposite, an imbalance of the lipidic composition of the retina leads to the degradation of the photoreceptors, and accumulation of deposits of debris made of lipids and lipoproteins, localized at the level of retinal pigment epithelium cells. Since photoreceptor outer segments have a high DHA content and require a constant supply of these omega 3 fatty acids due to their continuous renewal, diets rich in DHA may improve retinal function and protect against the development of exudative AMD (6, 8).

From a safety point of view, the only known side effects of omega 3 fatty acids are digestive intolerance and a modification of biochemical parameters related to platelet aggregation in human consuming very high quantities of omega 3 fatty acids. Numerous studies on omega 3 supplementation performed in the cardiovascular area involved thousands of patients without any significant side effects, particularly no haemorrhagic side effects. In the Gissi-Prevenzione study, 5000 patients aged 50 years or above had no increase in fatal or non-fatal stroke while they received PUFA together with aspirin. The American Food and Drug Administration (FDA) performed a comprehensive evaluation of more than 2600 articles on docosahexaenoic and eicosapentaenoic acids (DHA and EPA), the two long chain poly-unsaturated omega-3 fatty acids found in fish oil. The FDA concluded that dietary intakes of up to 3g daily of DHA and EPA were GRAS [generally recognized as safe] (21).

The safety profile of PUFA has been a strong argument to conduct a study with a nutritional supplement in elderly subjects who are often poly-medicated and more prone to adverse side effects with classical lipid-lowering drugs.

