Recently, DHA was given in patients affected with inherited retinitis pigmentosa, an inherited retinal degeneration. A slowing of the retinal degeneration was observed (visual function analyzed by ERG features) compared with the control group. No systemic nor retinal side effect was observed (22). Moreover, a preliminary study called NAT-1 was performed in thirty-eight patients affected with an homogeneous subgroup of AMD without CNV. Among them, 22 patients were orally given DHA at the dose of 480 mg per day in combination with EPA for 6 months. Neither adverse effect nor dropout were observed. It was shown that oral intake of DHA can significantly increase the levels in serum and red blood cell membranes, even in the elderly population (23). It is now interesting to evaluate the potential efficacy of oral supplementation of DHA in preventing the occurrence of new vessels in patients affected with AMD.

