### 6.1.3 Assessments of efficacy variables

### Primary efficacy variable

The occurrence of choroidal new vessels in the study eye will be determined from prospective assessment of fluorescein angiography every year.

Patients will be asked to report any new visual symptoms referable to the study eye between visits and to come back immediately for an angiography. Then a suitable laser or photodynamic therapy will be performed if any CNV have occurred.

Fluorescein angiography will allow to detect the presence and specify the location (extrafoveal, juxtafoveal, subfoveal), type (classic, occult) of CNV. It will be performed, through the dilated pupil, after intra-venous injection of 10% sodium fluorescein. This examination will be performed first on D0 for both eyes, then yearly.

If CNV are suspected in the study eye, an indocyanine green (ICG) angiography will be also performed to confirm their occurrence and characterize them precisely.

The protocol for fluorescein and ICG angiography is described in appendix I.C.

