### 6.2.2 Systemic tolerance

Fasting plasma lipoproteins profile [triglycerides (TG), total cholesterol (TC), HDL-C and

LDL-C] will be performed on D0, at the 6 month visit and at the 3 year visit. To this end blood samples after fasting will be taken. The protocol for dosage is described in appendix I.D. If any abnormality is noticed which was either not present at baseline or which was worse than at baseline, then the investigator will have to complete an adverse event form .

Moreover, all systemic adverse events, particularly digestive adverse events (nausea, eructations, diarrhea or abdominal pain) and bleeding events*, will be registered all along the study (see paragraph 6.2.3).

** because there is no simple, specific and accurate biologic index allowing to predict the risk for bleeding.*

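### The reading of CNV, on which the primary endpoint rests, is not kept apart from information that could hint at allocation

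*Protocol*

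**What the plan says.** **The endpoint.** Protocol section 6.1.3 states that CNV in the study eye "will be determined from prospective assessment of fluorescein angiography every year". ICG angiography follows if CNV is suspected, and patients with new symptoms return between visits for an extra angiogram. Neither that section nor Appendix I.C says who reads the angiograms or what the reader may know. Drusen images, by contrast, go to an outside laboratory for automatic quantification (section 6.1.3, Appendix I.B).

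**The masking.** The active product is described as "Capsules containing 600 mg of fish oil comprising 280 mg of DHA", three a day, so 3 x 600 mg = 1,800 mg of fish oil; the comparator is olive oil. Section 5.1 says "Both treatments will have identical presentation in order to preserve masking" and does not mention taste, odour or aftertaste.

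**What could hint at allocation.** The Introduction says "the only known side effects of omega 3 fatty acids are digestive intolerance", together with changes in platelet-related measurements at very high intakes. Section 6.2.2 asks for systemic events to be registered, "particularly digestive adverse events (nausea, eructations, diarrhea or abdominal pain" among them. Capsules and empty packs come back at each visit, and serum DHA is named as a compliance indicator (section 5.3). Section 6.1.2 uses DHA levels patient by patient.

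**Custody.** Section 5.2.2: "The double-masked treatment will be dispensed by the investigator or the pharmacist". Section 5.4: envelopes "containing the name of the allocated treatment, will be given to the investigator or the pharmacist".

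**The concern.** In a single-centre trial the same few people are likely to see the patient, hear the complaints, receive the capsules and look at the angiogram. Whether an early or doubtful lesion is called suspected CNV, and whether ICG is then ordered, has a threshold. If the person setting it has formed a view about allocation, the threshold can differ between arms, and the time to CNV then reflects that view as well as the treatment. The log-rank test cannot separate the two. The protocol relies on the capsules looking alike and does not add the usual second protection, a reader with no access to such information. This is trial conduct and belongs in the protocol rather than in an analysis plan.

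**Working it through.** **Step 1: the sections side by side.**

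| Information | When it arises | Kept from the CNV reader? |
| --- | --- | --- |
| Adverse events, including eructations (6.2.2, 6.2.3) | Every follow-up visit, from Month 6 | Not stated |
| Returned capsules and compliance (5.3) | Every visit | Not stated |
| Serum and red-cell DHA (5.3, 6.1.2) | Baseline, Month 6, Year 3 | Not stated |
| Code envelopes (5.4) | Throughout | Sealed, opaque, emergencies only |

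Scheduled angiography takes place at baseline and at Years 1, 2 and 3, not at Month 6 (section 6.3). So Month 6 complaints, and possibly Month 6 DHA results, can be known before the first follow-up reading.

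**Step 2: the plan's own figures.** Section 8.2 assumes 3-year CNV risks of 30% (placebo) and 15% (DHA), with 124 per group and a two-sided 5% test. Expected events are 124 x 0.30 = 37.2 and 124 x 0.15 = 18.6. The hazard ratio is ln(0.85)/ln(0.70) = 0.46. The plan's total of 245 is reproduced closely (244 by a Lachin-Foulkes log-rank calculation with one-year accrual, closure at 4 years and 20% exponential loss over 3 years). No figure in the plan is disputed here.

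**Step 3: illustration with no true effect.** Take 37 events per arm, D = 74. Suppose d false or borderline calls are added on placebo and d are missed on DHA. D is unchanged and the log-rank z shifts by s = d / sqrt(D/4) = d / sqrt(18.5) = d / 4.30. Two-sided rejection is Φ(s − 1.96) + Φ(−s − 1.96).

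| d each way | Eyes misclassified | s | Type I error |
| --- | --- | --- | --- |
| 0 | 0 | 0 | 5.0% |
| 1 | 2 | 0.23 | 5.6% |
| 2 | 4 | 0.47 | 7.5% |
| 3 | 6 | 0.70 | 10.7% |
| 5 | 10 | 1.16 | 21% |

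**Step 4: under-detection on DHA only.** If a fraction f of CNV on DHA is detected, the hazard ratio is ln(1 − 0.30f)/ln(0.70), events are 124 x 0.30 x (1 + f), and the shift is sqrt(events/4) x |ln HR|. For f = 0.90: HR 0.882, 70.7 events, type I error 8.2%. For f = 0.80: HR 0.769, 67.0 events, 18.9%.

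**Step 5: late rather than lost.** Steps 3 and 4 treat a missed CNV as never found, yet angiography is repeated yearly. A simulation with 124 per arm, 30% risk in both, yearly readings and no dropout gives about 5% if 8% of DHA-arm CNV is found one reading late, and between 5% and 6% if 13.5% is. Permanent misses at those rates give about 7% and 11%.

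**Step 6: under the planned effect.** Two calls each way turn 37 against 19 events into 39 against 17. The hazard ratio moves from ln(1 − 19/124)/ln(1 − 37/124) = 0.47 to ln(1 − 17/124)/ln(1 − 39/124) = 0.39.

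**The case against.** The case for leaving the text alone has substance. No reader is named, so that the investigator reads the angiograms is an inference, though a natural one. A reader might also infer that fish oil reveals itself through eructations. The protocol does not say that these taste of fish or differ by arm; they are one of four digestive events listed, capsules are swallowed with water at mealtimes, and of the pilot the Introduction says "Neither adverse effect nor dropout were observed". That pilot treated 22 patients with 480 mg DHA for 6 months, against 840 mg for 3 years here, so it reassures only in part.

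It is also tempting to read envelope custody as knowledge of allocation. It is not: the envelopes are sealed and opaque, there is one for each patient, and they may be opened only in an emergency with reasons given. Numbered packs reveal nothing when handed out. Section 6.2.3 requires neutral questioning about adverse events. A false CNV call would have to survive ICG and would lead to treatment, which is a high threshold.

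Two further inferences fail. The primary endpoint is not the only one exposed: visual acuity is measured by an examiner (section 6.1.3), and the slit-lamp findings and lens grading are human assessments too (section 6.2.1, Appendix I.F). Nor is the bias beyond later remedy: images are archived (section 7.3, Appendix I.C), so a masked re-read would be possible, although it could not supply an angiogram or ICG that was never taken.

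What survives all this is the gap itself: no section separates the CNV reading from the information in step 1.

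**Conclusion.** The point holds as a gap in section 6.1.3. The primary endpoint is a human judgement, and the protocol does not protect it from information that could hint at allocation. The documents do not show that unmasking will occur, and they give no figure for its size. The calculations show only that few eyes would matter: type I error of about 7.5% with two miscalls each way and about 11% with three. They assume that every miscall favours DHA, that missed CNV stays missed, and that the 30% risk holds in both arms; with detection merely delayed by one reading, the increase is one percentage point or less in the cases tried. The change is worth making because it costs little and is best settled before the first reading.

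**What to change.** 1. **Section 6.1.3:** require that CNV status (absent, suspected with ICG ordered, or present) is read from the angiogram images and signed before that visit's adverse events, capsule returns or compliance are seen. Where possible the reader should be an ophthalmologist already on site who does not collect adverse events or capsules from that patient. Order within the visit is not enough alone, because earlier complaints, for example at Month 6, would already be known.
2. **Sections 5.3 and 6.2.3:** have the CIC study nurse, who already coordinates logistics (section 7.1), collect capsule returns and the routine adverse-event answers.
3. **Sections 5.2.2 and 5.4:** name the hospital pharmacist alone for dispensing and envelope custody, with emergency access kept.
4. **Sections 5.3 and 6.1.2:** withhold serum and red-cell fatty-acid results from the CNV reader until database lock. The lipoprotein results that the investigator needs for adverse-event reporting are unaffected.

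The cost is protocol wording, a fixed order of steps within the visit, some reading time from a second ophthalmologist where one is available, and a pharmacy that can be reached for emergency code-breaking. Sample size, tests and visit schedule do not change. One route stays open: angiograms between visits depend on patients reporting symptoms, so a patient's own guess at allocation could still affect when CNV is found.
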